#### Experimental arm – VR-based training scenarios

VR is employed for a dual therapeutic purpose:

simulating feared, anxiety-evoking scenarios, thereby enabling both assessment and training of situationally induced anxiety and progressively promoting desensitization to anxiety-provoking stimuli;delivering an ACT-consistent mindfulness training targeting psychological flexibility processes (e.g., contact with the present moment, cognitive defusion, and acceptance), eliciting a grounding response within a digitally generated and safe environment.

VR sessions are divided into three sequential phases (total duration approximately 15 min): Adaptation, Exposure, and Relaxation (Fig. 3).

Adaptation phase (5 min): Participants are guided through brief relaxation and grounding exercises and are familiarized with the VR equipment. Procedures for operating the devices (described in subsequent sections) are explained, and participants are encouraged to become comfortable in the immersive environment to facilitate engagement and reduce novelty-related discomfort during subsequent phases.

Exposure phase (5 min): This phase constitutes the core component of the VR-based intervention. Participants are exposed to simulated public speaking situations embedded within an examination context. Across sessions, task difficulty and social-evaluative stress are gradually increased through systematic manipulation of virtual characters (e.g., number and behavior of avatar instructors and audience members). This graded exposure supports progressive acquisition and practice of skills to manage anxiety and stress related to examinations.

Relaxation phase (5 min): This phase is dedicated to mindfulness practice and rebalancing, aiming to reduce stress accumulated during exposure. Mindfulness practice supports inner awareness and improves emotion and stress management. The relaxation component also facilitates consolidation of the intervention’s effects on anxiety and stress regulation.

#### VR-ACT training

The VR-ACT experience takes place in a 360° immersive 3D naturalistic woodland environment (Fig. 3c), surrounded by trees and natural elements designed to evoke calm and grounding. Dynamic interactive features—such as breath-synchronized fog, ambient nature-based auditory stimuli, and subtle continuous movements of light, leaves, and grass—enhance engagement and perceived presence during a semi-structured mindfulness training session. The session targets ACT psychological flexibility processes and fosters feedback-based coordination between participants and the virtual setting, promoting self-regulation and adaptive learning of psychological responses aligned with each targeted mindfulness skill. Phase duration is determined by the operator, allowing exploration of different options within each phase and enhancing flexibility of the immersive experience.

#### VR-ERP

VR-ERP uses 360° 3D videos depicting scenarios such as an exam classroom and an auditorium within a university campus (Fig. 3a–b). Across sessions, variables such as audience size and behavior, professor characteristics, attire (formal vs. informal), and examination committee composition vary. Scenarios are presented according to a gradual hierarchy of challenge; at the student’s discretion, specific scenarios are repeated. Scenarios are selected based on distressing contents identified in the research-intervention literature [29]. During simulations, participant interactions influence the subsequent course of the exposure scenario. Each scenario follows a graded increase in exposure intensity, culminating in an oral exam involving a PowerPoint presentation in the final exposure. Each VR-ERP session is preceded by a VR-ACT session and followed by a 10-minute debriefing intervention providing supportive feedback and guidance to consolidate skills acquired during exposure.

Familiarization session: in the session participants receive a standardized explanation of the VR program’s aims and procedures. They are introduced to the Oculus Quest 3, a consumer-grade standalone VR system consisting of a head-mounted display (HMD) and two handheld controllers. After donning the headset, they complete a brief 5-minute familiarization session to learn basic controls and navigation. This training supports acclimatization to the VR environment, facilitates graded exposure to performance-related stressors, and promotes adaptive regulation of physiological and affective responses within a controlled yet ecologically valid simulation.

Baseline session: the session establishes a physiological reference point preceding implementation of the training. The configuration elicits a controlled anxiogenic response associated with judgment, self-presentation, and evaluation expectancy. Physiological measures provide a baseline stress reactivity index under standardized conditions and support subsequent assessment of training-related modulation of autonomic responses.

Training Condition 1: The condition introduces the exam-related context in a minimally threatening and highly controlled manner. The configuration presents the student and professor within an examination room (Fig. 3, top row, first column), while the interaction remains informal and limited to non-evaluative questions. The condition elicits mild activation of evaluative schemas, allowing engagement with oral exam cues without triggering a marked anxiogenic response. The focus remains on encouraging adaptive self-regulation and facilitating habituation to interpersonal and environmental components of the scenario. By reducing perceived pressure and discouraging avoidance or neutralizing strategies, this phase provides a foundational step toward more complex and emotionally salient training conditions.

Training Condition 2: The condition intensifies exposure to social-evaluative cues within the examination context. The scenario occurs in an exam room and includes the student, the professor, and an audience of approximately ten observers (Fig. 3, top row, middle column). Attire remains informal, but the interaction shifts to actual exam-related questions, increasing perceived performance demands. This configuration amplifies engagement with social evaluation and performance pressure while preventing neutralization and covert avoidance behaviors. Sustained exposure under controlled but more challenging conditions supports physiological habituation and consolidation of adaptive behavioral self-regulation, preparing participants for higher-intensity exposures in subsequent phases.

Training Condition 3: The condition maximizes exposure to high-intensity social-evaluative demands within a formal examination setting. The session takes place in a large lecture hall and involves the student, professor, and a broader audience (Fig. 3, middle column, middle row). All characters wear formal attire, and the interaction centers on actual exam questions, increasing realism and performance salience. This configuration facilitates extinction of phobic responses and promotes development of adaptive coping strategies within a highly interactive, evaluatively charged environment. The condition encourages expansion of the behavioral repertoire and implementation of active self-regulation strategies. As the most demanding phase of the protocol, it supports consolidation of robust and context-generalizable regulation skills.

Training Condition 4: The condition promotes generalization and consolidation of responses acquired in preceding phases and tests whether self-regulation skills, coping strategies, and reduced anxiety responses extend to a related but distinct high-salience social performance context. The condition takes place in a large lecture hall and is framed by a formal examination atmosphere. The scenario includes the student, professor, examination committee, and an audience. The task shifts from answering exam questions to delivering a presentation, introducing a different performance format. This configuration requires autonomous organization, sustained delivery, and direct engagement with an evaluative audience, providing a stringent test of stability and transferability of learned regulatory processes.

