### Interventions

#### Participants

Participants in the control group do not receive VR training but follow the same assessment schedule as the experimental group. Specifically, they complete baseline (T0), post-intervention (T1), and follow-up (T2) evaluations using the same psychological measures. This design allows comparison between intervention and control conditions, thereby isolating the effects of VR training from potential confounding factors such as time and repeated testing effects.

The experimental intervention includes two distinct VR-based training components: (A) VR-ERP, which gradually exposes students to anxiety-provoking situations to prevent avoidance responses, and (B) VR-ACT training, which provides consistent mindfulness practice aimed at enhancing psychological flexibility and value-oriented behaviors. After completing VR-ACT training, participants in the experimental group proceed to a standard counseling intervention.

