### Statistical analyses

All statistical analyses are conducted using IBM SPSS Statistics (version 29.0) and follow a pre-specified analytic strategy designed to evaluate changes in psychological and physiological outcomes across the study period and to compare the effectiveness of standard counseling with and without VR-based exposure. Descriptive statistics are first computed to characterize the sample to assess baseline equivalence between groups. Reliability analyses (Cronbach’s α and McDonald’s ω) are performed to confirm the internal consistency of the psychometric instruments.

Because the study involves repeated assessments at baseline (T0), post-intervention (T1), and follow-up (T2), the primary analyses use linear mixed-effects models, an approach well suited to handling longitudinal data and missing observations. These models test for the main effects of time and group, as well as the critical time × group interaction, indicating differential improvement between the VR-enhanced counseling condition and the control group. Where significant interactions emerge, post hoc comparisons with Bonferroni adjustment are conducted to identify specific temporal patterns of change. Complementary analyses of change scores (ΔT1–T0 and ΔT2–T0) are performed using independent-sample t-tests or, where assumptions are violated, Mann–Whitney U tests; General Linear Models including baseline variables and demographic covariates further clarify group differences in treatment response.

Physiological data collected during VR sessions (including heart rate, HRV, and electrodermal activity) are examined through mixed models and event-based analyses aligned with the structure of the VR exposure tasks, allowing evaluation of both arousal patterns and recovery processes. Exploratory regression models are used to identify predictors of treatment benefit, such as baseline symptom severity or physiological reactivity during VR exposure.

Missing data are handled through the mixed-model framework, which accommodates incomplete longitudinal data; if dropout shows non-random patterns, multiple imputation is applied as a sensitivity check. For all analyses, statistical significance is set at α = 0.05, with appropriate corrections for multiple comparisons.

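### Exposure intensity and task change across sessions by design, so change in exposure-phase physiology from the baseline VR run mixes training effect with stimulus effect, and the bias can go either way

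*Protocol article*

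**What the plan says.** The VR-ERP section describes a baseline session, held before training, that is meant to provoke anxiety in a controlled way. Its stated use is: "Physiological measures provide a baseline stress reactivity index under standardized conditions and support subsequent assessment of training-related modulation of autonomic responses". The Statistical analyses section opens with a strategy "designed to evaluate changes in psychological and physiological outcomes across the study period". Under Physiological assessment, recording runs from Session 1, labelled T0 and baseline, to Session 4, labelled T1.

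The stimulus is graded. In the section on the experimental arm: "Across sessions, task difficulty and social-evaluative stress are gradually increased through systematic manipulation of virtual characters". VR-ERP then sets out four conditions. Condition 1 keeps threat low and is described as not provoking marked anxiety. Condition 2 adds about ten observers and real exam questions. Of Condition 3 it says: "As the most demanding phase of the protocol, it supports consolidation of robust and context-generalizable regulation skills". Condition 4 replaces the oral exam with a presentation, "providing a stringent test of stability and transferability of learned regulatory processes".

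The only repetition described is at the student's own choice ("discretion, specific scenarios are repeated"). Under Interventions, Participants: "Participants in the control group do not receive VR training but follow the same assessment schedule as the experimental group".

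**The concern.** A before-and-after reading of reactivity needs the same challenge at both times. Here the challenge itself is the graded treatment. A difference in heart rate, HRV or electrodermal activity between the baseline run and a later exposure could come from training, from a harder or easier scenario, or from both. No scheduled re-presentation of a fixed scenario is described. The control arm has no exposure-phase response to subtract.

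At stake is a secondary conclusion. The trial could report a training effect on autonomic response that is only an easier stimulus, or miss a real one because the later stimulus is harder.

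**Working it through.** The plan gives no figure for this contrast, and its sample-size calculation does not bear on it. The check compares the described configurations, then shows what can be separated and in which direction the bias runs.

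**Inputs (VR-ERP section)**

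| Run | Room | Audience | Style | Task |
|---|---|---|---|---|
| Baseline | not given | not given | not given | anxiety-provoking, detail not given |
| Condition 1 | exam room | none beyond the professor | informal | non-evaluative questions |
| Condition 2 | exam room | about 10 | informal | exam questions |
| Condition 3 | large lecture hall | larger | formal | exam questions |
| Condition 4 | large lecture hall | committee and audience | formal | presentation |

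Conditions 1 and 3 differ in four stated features: room, audience, formality and question type. The order 1 < 2 < 3 is the article's own. The baseline's place in that order is not given, except that it is called anxiety-provoking while Condition 1 is said not to be markedly so.

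**Step 1: can occasion and intensity be separated?** Assume one configuration per occasion (baseline, then Conditions 1 to 4) and intensity scores of 1 to 4 for the conditions. Five occasion indicators plus one intensity column make 6 columns. The matrix has rank 5 for any baseline score from 1 to 4, so the intensity effect cannot be told apart from the occasion effects. With Conditions 1 to 4 alone and a straight-line session trend, the matrix of intercept, session and intensity has rank 2 of 3. Adding the baseline to the straight-line model gives rank 3 of 3, but separation then depends on the baseline's score, which the article does not give.

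**Step 2: sign of the bias.** Let h be the training effect per occasion, b the effect of one intensity step, I(k) the score of Condition k, and x the score of the baseline. Then:

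observed change at Condition k = h·k + b·(I(k) − x), so bias = b·(I(k) − x).

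With b = +0.2 SD (assumed) and I = 1, 2, 3, 4:

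| Baseline score x | Cond. 1 | Cond. 2 | Cond. 3 | Cond. 4 |
|---|---|---|---|---|
| 1 | 0 | +0.2 | +0.4 | +0.6 |
| 2 | −0.2 | 0 | +0.2 | +0.4 |
| 3 | −0.4 | −0.2 | 0 | +0.2 |
| 4 | −0.6 | −0.4 | −0.2 | 0 |

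A negative entry exaggerates a fall; a positive entry hides one.

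- True effect h = −0.2 (assumed), x = 2: true changes are −0.2, −0.4, −0.6, −0.8. Observed changes are −0.4 at every condition: overstated at Condition 1, correct at Condition 2, masked at Conditions 3 and 4.
- No training effect (h = 0), x = 2: Condition 1 still shows a false fall of −0.2.
- x = 4: no masking anywhere, and overstatement at Conditions 1 to 3.
- Range: with b from 0.1 to 0.3 and x = 2, the bias at Condition 1 is −0.1 to −0.3 and at Condition 4 is +0.2 to +0.6. Scoring Condition 4 equal to Condition 3 lowers the last column of the table by 0.2.

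**Step 3: what is left to compare.** Like-for-like comparisons exist only where a student chose to repeat a scenario, and those repeats are self-selected.

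**The case against.** The best defence has three parts.

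First, Session 1 to Session 4 change is not a named endpoint. The sentence about the baseline states a purpose, no section commits to a contrast that ignores the scenario, and model terms for intensity belong in a full plan that a condensed article need not reproduce. It is true that no endpoint is named, and leaving out model terms is not the fault. The difficulty lies in the stated use of the baseline combined with the schedule: a later model cannot reliably recover a same-configuration comparison that the design never schedules.

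Second, settings are time-stamped (VR materials), scenarios can change during a session, and event-based analyses are planned. Intensity thus also varies within sessions, and some adjustment may be possible. This stands to that extent: the exact aliasing in Step 1 needs one configuration per occasion, and the article describes five configurations but four recorded sessions without mapping one to the other. Logging does not, however, guarantee separation when intensity rises with session order.

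Third, graded exposure is the treatment. That stands fully. Grading is sound; the difficulty is using the graded series as its own yardstick.

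**Conclusion.** The point holds in a limited form. As written, exposure-phase change from the baseline run, or across sessions, in the experimental arm confounds training with stimulus. The size cannot be fixed from the article; the SD values above are illustrations on assumed effects.

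A reader might infer that the design will mostly hide habituation, since later sessions are harder. The document does not support that. The baseline is anxiety-provoking and Condition 1 is milder, so the first contrast leans towards a false fall. At Conditions 3 and 4 masking occurs only if the baseline is milder than they are, which is not stated.

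A reader might also infer that the main results are at risk. They are not: the PRPSA and STAI comparisons do not use these recordings, and the within-session arousal and recovery aim is not shown to be affected. What is affected is one secondary reading, worth correcting because the remedy is mostly wording.

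**What to change.** In VR-ERP and Statistical analyses, state that a training effect on autonomic reactivity is claimed only from comparisons at the same configuration. Report all other exposure-phase values by scenario, descriptively, with no training-effect claim. Leave the within-session analyses as planned.

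If a reactivity claim is wanted, re-run the unchanged baseline configuration after the last condition and make that the contrast. Report it as a within-arm change, because controls have no counterpart. The cost is about 5 minutes and one more anxiety-provoking exposure per experimental participant.

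Adaptation-phase values may be reported over a fixed window, as resting or anticipatory arousal only. That phase is not a clean constant: "Participants are guided through brief relaxation and grounding exercises and are familiarized with the VR equipment". Equipment novelty fades and anticipation of harder sessions may grow, so both need a caveat. The fixed window matters because the VR-ACT training section lets the operator set phase duration.

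The wording change needs no new data. Its downside is that, without the re-run, the trial makes no claim about training-related change in reactivity to exposure.

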**Fig. 3 Fig3:**
[figure not shown]
Representative first-person views from the VR application. Top row: classroom scene with low audience density, full audience, and view of the professor. Middle row: user view from the lectern, front view of the lecture hall audience, position of the professor relative to user. Bottom row: forest relaxation environment showing progressive fog proximity used for respiration-synchronized mindfulness guidance

### Statistical analyses

All statistical analyses are conducted using IBM SPSS Statistics (version 29.0) and follow a pre-specified analytic strategy designed to evaluate changes in psychological and physiological outcomes across the study period and to compare the effectiveness of standard counseling with and without VR-based exposure. Descriptive statistics are first computed to characterize the sample to assess baseline equivalence between groups. Reliability analyses (Cronbach’s α and McDonald’s ω) are performed to confirm the internal consistency of the psychometric instruments.

Because the study involves repeated assessments at baseline (T0), post-intervention (T1), and follow-up (T2), the primary analyses use linear mixed-effects models, an approach well suited to handling longitudinal data and missing observations. These models test for the main effects of time and group, as well as the critical time × group interaction, indicating differential improvement between the VR-enhanced counseling condition and the control group. Where significant interactions emerge, post hoc comparisons with Bonferroni adjustment are conducted to identify specific temporal patterns of change. Complementary analyses of change scores (ΔT1–T0 and ΔT2–T0) are performed using independent-sample t-tests or, where assumptions are violated, Mann–Whitney U tests; General Linear Models including baseline variables and demographic covariates further clarify group differences in treatment response.

Physiological data collected during VR sessions (including heart rate, HRV, and electrodermal activity) are examined through mixed models and event-based analyses aligned with the structure of the VR exposure tasks, allowing evaluation of both arousal patterns and recovery processes. Exploratory regression models are used to identify predictors of treatment benefit, such as baseline symptom severity or physiological reactivity during VR exposure.

Missing data are handled through the mixed-model framework, which accommodates incomplete longitudinal data; if dropout shows non-random patterns, multiple imputation is applied as a sensitivity check. For all analyses, statistical significance is set at α = 0.05, with appropriate corrections for multiple comparisons.

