## Method

### Aim

We adopt a two-arm randomized controlled trial (RCT) design to investigate whether VR-delivered controlled exposure can complement standard psychological counseling in addressing PSA and general anxiety symptoms among students accessing the UPCS. The findings are expected to provide evidence regarding the effectiveness of integrating VR-based exposure as an adjunct to Exposure and Response Prevention–Acceptance and Commitment Therapy (ERP-ACT) within counseling to manage anxiety and stress in university students.

It is hypothesized that:

Primary Outcome - Students receiving brief psychological counseling supported by ERP and ACT training combined with VR-based exposure exhibit significantly greater reductions in PSA and anxiety levels from baseline (T0) to post-intervention (T1), compared with students receiving standard psychological counseling alone.Secondary Outcome - The two VR components (ERP and ACT) are expected to exert differential effects. Specifically, the relaxation modules should primarily reduce physical tension and physiological arousal, whereas the immersive exposure modules should mainly target the psychological aspects of public speaking, leading to lower fear and reduced perceived mental effort during performance-related scenarios. Physiological data are continuously recorded during each intervention session to assess patterns of arousal and recovery and to examine whether VR-supported counseling is associated with different within-session responses compared with counseling alone.Other Pre-specified Outcome - These benefits are expected to be maintained over time; therefore, students in the VR-ERP and VR-ACT training conditions are expected to continue to exhibit better outcomes at the 3-months follow-up assessment (T2), compared with students receiving standard counseling alone.

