#### Physiological assessment

The EmbracePlus wristband is a research-grade, wrist-worn wearable device designed to continuously monitor a range of physiological parameters, providing real-time access to raw sensor data suited for scientific, clinical, and real-world studies. Its built-in sensors include photoplethysmography (PPG) for blood volume pulse (BVP), from which heart rate (HR), inter-beat interval (IBI), and heart rate variability (HRV) are derived, electrodermal activity (EDA or skin conductance) as an index of autonomic arousal, a 3-axis accelerometer to track motion and activity, and a peripheral skin-temperature sensor. The device samples EDA at 4 Hz and PPG at 64 Hz, and it has demonstrated high correlations with clinical-grade equipment for HR and HRV under controlled conditions (though less so for EDA under movement) [26]. Thanks to its wrist-worn design, on-board data storage, and Bluetooth syncing capabilities, the EmbracePlus enables extended ambulatory monitoring of physiological responses in naturalistic settings, enabling studies of stress, emotion, cognitive load, and behavioral states in real time. Data were collected during four intervention sessions, from Session 1 (T0; baseline) to Session 4 (T1), corresponding to the end of the 4-week intervention period.

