A dedicated PC-based control software application, developed using Microsoft Visual Studio, allows the experimenter to monitor, manage, and customize the VR session in real time. Through this interface, the experimenter can configure multiple key experimental parameters, including:

the type of virtual environment (e.g., classroom or lecture theatre);the number of virtual audience members;the general structure and difficulty of the speaking or examination task.

The control software communicates bidirectionally in real time with the VR application, enabling the dynamic delivery and modulation of stimuli, questions, and scenario changes during the session. All experimental parameters are automatically time-stamped and logged for subsequent analysis. The control software integrates with OpenAI’s language model through an Application Programming Interface (API), enabling the dynamic and personalized generation of examination questions. The experimenter can enter high-level natural language prompts describing the participant’s academic background (e.g., *“Ask the student about a second-year engineering class”*). The language model then generates a contextually appropriate academic question, which is transmitted in real time to the VR application and delivered verbally by the virtual professor to the participant. This approach enables:

high variability and adaptability of task content;personalization based on participant characteristics and academic context;increased ecological validity of the simulated social interaction.

All input prompts and corresponding AI-generated examination questions are automatically stored and time-stamped in the system log for later quantitative and qualitative analyses.

During each VR session, participants wear a medical-grade wrist-worn biometric device (EmbracePlus), part of the Empatica Health Monitoring Platform. The system continuously records multiple physiological parameters associated with stress and emotional arousal, including:

heart rate (HR);heart rate variability (HRV);electrodermal activity (EDA);skin temperature;movement and activity levels.

The biometric device operates independently from the VR system but is time-synchronized with the experimental software, ensuring precise temporal alignment between physiological signals and VR events. Both the VR application and the PC-based control software automatically generate detailed time-stamped log files, including:

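### The secondary physiological comparison cannot support a between-arm treatment claim: the sections disagree on whose data are analysed, no stimulus is common to both arms, and its T0 falls after allocation

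*Protocol article*

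**What the plan says.** All references are to the protocol article.

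- **Aim.** Under the secondary outcome, physiology is recorded in every intervention session in order to "examine whether VR-supported counseling is associated with different within-session responses compared with counseling alone". That is a between-arm aim.
- **Statistical analyses.** "Physiological data collected during VR sessions (including heart rate, HRV, and electrodermal activity) are examined through mixed models and event-based analyses". The latter are "event-based analyses aligned with the structure of the VR exposure tasks". Exploratory models for predictors of benefit include "physiological reactivity during VR exposure".
- **VR materials.** "During each VR session, participants wear a medical-grade wrist-worn biometric device (EmbracePlus").
- **Design and setting; Table 1.** Recording takes place in each session (Design and setting), and the physiological row of Table 1 is ticked for Weeks 1 to 4. Neither limits this to one arm.
- **Physiological assessment.** "Data were collected during four intervention sessions, from Session 1 (T0; baseline) to Session 4 (T1"), again with no arm named.
- **Participants and recruitment.** T0 measures are finished before the allocation is opened.
- **VR-ERP and the VR-based training scenarios.** Intensity increases over sessions: "Each scenario follows a graded increase in exposure intensity, culminating in an oral exam involving a PowerPoint presentation in the final exposure".

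**The concern.** A between-arm comparison needs the same quantity measured in both arms under comparable conditions, with a starting value that treatment has not touched. The physiological plan does not secure any of these. Heart rate, HRV and electrodermal activity respond to what the participant is facing at that moment, and the protocol relies on this: VR materials treats audience size as a key stressor and wants physiological variation to be attributable to the experimental manipulation. If one arm faces a simulated examination and the other sits in a counseling session, a group difference may say more about the scene than about any therapeutic effect. The same holds over time in the VR arm, where later sessions are harder by design. A significant group, time or interaction effect on physiology could then be reported as evidence on mechanism or benefit when the data cannot separate these explanations.

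**Working it through.** **1. Whose data?** Two groups of statements stand side by side.

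| Section | Recording or analysis | Arm restriction |
|---|---|---|
| Aim | each intervention session | none; comparison with counseling alone intended |
| Design and setting | each session | none |
| Physiological assessment | four intervention sessions | none |
| Table 1, physiological row | Weeks 1 to 4 | none (the intervention rows are labelled by arm) |
| VR materials | each VR session | VR arm by implication |
| Statistical analyses | data from VR sessions, events tied to VR tasks | VR arm by implication |

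The Interventions section says that controls get no VR and keep the same assessment schedule, but the measures it names for them are psychological. Read with the last two rows, there are no control data to compare. Read with the first four, control data exist, but from sessions without the VR stimulus, and the event-based analysis has no control counterpart. Neither reading yields a comparison under a common stimulus.

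**2. Is physiological T0 a baseline?** Physiological assessment sets T0 at intervention Session 1. Table 1 places Week 1 (T0) after the Allocation column and ticks VR-ERP and VR-ACT in it. Participants and recruitment places T0 measures before allocation is opened. For the questionnaires this is consistent, because Table 1 ticks them at enrolment. For physiology it is not: its T0 is after allocation and in a treatment week. VR-ERP also describes a baseline session that precedes training. It sits in the VR arm's intervention text, uses an anxiety-eliciting configuration and has no column of its own in Table 1, so it does not supply a pre-allocation reference for both arms.

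**3. What does Session 1-to-4 change contain?** The VR-based training scenarios section raises social-evaluative stress across sessions. In VR-ERP, the last condition replaces exam questions with a presentation. Change in the VR arm is therefore the training effect plus the effect of a different stimulus and task. No common test stimulus is named. Yet VR-ERP says the baseline session should support later assessment of how training modulates autonomic responses.

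**4. Predictors of benefit.** Reactivity during VR exposure exists in one arm only. It can be correlated with outcome in that arm, but it cannot show who gains more from VR than from counseling alone.

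**5. Size.** The plan gives no physiological effect or SD. Its one relevant figure is the sample size for the psychological change score: d = 0.75, two-sided α = 0.05. For a two-sample t-test with noncentrality d·√(n/2) and 2n − 2 degrees of freedom, n = 29 per arm gives power 0.801 and n = 28 gives 0.787, so the stated 29 is reproduced. Dropout: 29/(1 − 0.20) = 36.25, against the stated 36. This calculation does not involve physiology.

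As an illustration only, assume that both arms are recorded, that a Session 4 minus Session 1 change is compared between arms, that training has no effect on reactivity, and that the rising stimulus alone shifts the VR arm's mean change by s SD. The same formula with s in place of d gives the chance of rejecting at a nominal 5%:

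| s (assumed) | n = 29 per arm | n = 36 per arm |
|---|---|---|
| 0 | 5.0% | 5.0% |
| 0.2 | 11.6% | 13.3% |
| 0.3 | 20.2% | 24.1% |
| 0.5 | 46.5% | 55.3% |
| 0.75 | 80.1% | 88.1% |

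Neither s nor this exact contrast is in the document. The table shows only that a modest stimulus-driven shift would matter at this sample size.

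**The case against.** The case on the other side has several parts.

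- **Control recording is not ruled out.** Four places imply it, and VR materials describes the VR system rather than excluding controls. This stands. A reader might infer that controls are never recorded; the document supports only a contradiction that must be resolved.
- **No Session 1-to-4 between-arm test is spelled out.** The time, group and interaction terms are attached to T0, T1 and T2, and physiology has no T2. The aim speaks of association, and for a purely descriptive aim the different stimulus is part of the intervention. This stands in part. However, the opening of Statistical analyses covers change in physiological as well as psychological outcomes, alongside comparing the two treatments, and nothing confines the physiological result to description.
- **The direction of distortion is unknown.** A reader might infer that sessions run from a mild start to a hard finish, so that real habituation would look like worsening. That requires T0 to be the first, informal training condition. If T0 is the anxiety-eliciting baseline session, the start is not mild.
- **Session and scenario need not coincide.** A reader might infer that they are almost perfectly collinear, or that a baseline session and four training conditions cannot fit into four sessions. No section assigns one condition to one session, scenarios may be repeated as the student wishes, and the experimenter can set room, audience size and difficulty. Neither inference is shown.
- **Part of the remedy is in place.** Scenario parameters are already logged with timestamps and the event-based analysis is aligned with the tasks. This helps within the VR arm, but it creates no common stimulus across arms.
- **The predictor models are labelled exploratory.** True, so that part is a matter of wording and interpretation.

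**Conclusion.** The concern holds in a limited form. As written, the secondary physiological comparison cannot support a claim that VR changed arousal or recovery relative to counseling alone. Three things carry this: the sections conflict on whose data are recorded and analysed; if controls are recorded, no stimulus is common to both arms; and the physiological T0 is a post-allocation intervention session, whereas elsewhere T0 precedes the opening of the allocation. In addition, Session 1-to-4 change in the VR arm mixes training with stimulus level and task format.

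The size and direction of the distortion cannot be derived from the document, and the rejection rates above rest on an assumed shift. It would go too far to call all the physiological work invalid: description of arousal and recovery within the VR arm remains sound. The primary PRPSA/STAI analysis and the sample size are not affected. The change should be made because it alters what the trial may conclude on a stated secondary outcome, but it does not threaten the main result.

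**What to change.** 1. Reconcile Aim, Design and setting, Physiological assessment and Table 1 with VR materials and Statistical analyses: state which arms wear the band, in which sessions, and which segments are analysed.
2. Do not use Session 1 under VR as a pre-treatment baseline. Reconcile the two uses of T0, and say where the baseline session described under VR-ERP falls in Table 1.
3. Analyse VR-phase physiology within the VR arm only, with logged scenario, audience size and movement as covariates. Do not read Session 1-to-4 change as a treatment effect.
4. Restrict any between-arm physiological statement to description of counseling segments that both arms have, or drop it. The Interventions section has experimental participants go on to counseling after VR-ACT, so note that arousal from VR may carry over into that segment.
5. Call reactivity during VR exposure a within-arm correlate of outcome. Test predictors of benefit over counseling only as baseline variable × group.

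**Cost.** If both arms already wear the band, this is wording plus use of logs and movement data that the system already collects. If controls do not, adding them changes trial conduct, and sessions already held cannot be recovered; recruitment is expected to finish by December 2026, so this should be settled early. The scientific price is that no between-arm claim about exposure-phase arousal can be made.
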